## Abstract

**Background:**

After an initial attack of biliary pancreatitis, cholecystectomy minimizes the risk of recurrent biliary pancreatitis and other gallstone-related complications. Guidelines advocate performing cholecystectomy within 2 to 4 weeks after discharge for mild biliary pancreatitis. During this waiting period, the patient is at risk of recurrent biliary events. In current clinical practice, surgeons usually postpone cholecystectomy for 6 weeks due to a perceived risk of a more difficult dissection in the early days following pancreatitis and for logistical reasons. We hypothesize that early laparoscopic cholecystectomy minimizes the risk of recurrent biliary pancreatitis or other complications of gallstone disease in patients with mild biliary pancreatitis without increasing the difficulty of dissection and the surgical complication rate compared with interval laparoscopic cholecystectomy.

**Methods/Design:**

PONCHO is a randomized controlled, parallel-group, assessor-blinded, superiority multicenter trial. Patients are randomly allocated to undergo early laparoscopic cholecystectomy, within 72 hours after randomization, or interval laparoscopic cholecystectomy, 25 to 30 days after randomization. During a 30-month period, 266 patients will be enrolled from 18 hospitals of the Dutch Pancreatitis Study Group. The primary endpoint is a composite endpoint of mortality and acute re-admissions for biliary events (that is, recurrent biliary pancreatitis, acute cholecystitis, symptomatic/obstructive choledocholithiasis requiring endoscopic retrograde cholangiopancreaticography including cholangitis (with/without endoscopic sphincterotomy), and uncomplicated biliary colics) occurring within 6 months following randomization. Secondary endpoints include the individual endpoints of the composite endpoint, surgical and other complications, technical difficulty of cholecystectomy and costs.

**Discussion:**

The PONCHO trial is designed to show that early laparoscopic cholecystectomy (within 72 hours) reduces the combined endpoint of mortality and re-admissions for biliary events as compared with interval laparoscopic cholecystectomy (between 25 and 30 days) after recovery of a first episode of mild biliary pancreatitis.

**Trial registration:**

Current Controlled Trials: ISRCTN72764151

## Background

Acute pancreatitis is a major healthcare problem. The disease is the third most common gastrointestinal reason for acute hospital admission, carrying a mortality rate of 5% with a total annual cost of $2.2 billion in the USA alone [1,2]. In most western countries approximately 30 to 55% of cases are caused by gallstones or sludge, referred to as biliary pancreatitis [3]. After biliary pancreatitis, patients may experience a recurrent episode of biliary pancreatitis or other biliary events, such as acute cholecystitis, common bile duct obstruction, cholangitis or biliary colics [4,5]. In order to prevent these recurrent biliary events, international guidelines advise performing cholecystectomy or endoscopic sphincterotomy (ES) after biliary pancreatitis [6,7]. Failure to provide definitive treatment exposes the patient to (potentially fatal) risks of biliary diseases [8].

The timing of cholecystectomy in patients with clinically severe pancreatitis, with local complications such as pancreatic necrosis and organ failure, is deliberately delayed until local complications have resolved, typically after some 6 weeks [9].

In patients with mild pancreatitis, international guidelines advise cholecystectomy directly after recovery or in the first 2 to 4 weeks after discharge for mild biliary pancreatitis [4,6,7,10,11]. However, there is no consensus on the ideal moment of cholecystectomy. Audits from Germany, the UK, the USA and Italy report that the majority of specialists perform an interval cholecystectomy 6 to 12 weeks after discharge, due to uncertainty about the efficacy and safety of an early cholecystectomy and for logistical reasons [12-15]. In a nationwide study in the Netherlands, we demonstrated that three-quarters of the patients admitted with mild biliary pancreatitis underwent cholecystectomy a median of 6 weeks after discharge [16]. Comparable results were found in a systematic review by our group where over 50% of patients underwent cholecystectomy at least 6 weeks after discharge [17].

Several nonrandomized studies in patients with mild biliary pancreatitis suggested that early cholecystectomy, as compared with interval cholecystectomy, prevents recurrent biliary pancreatitis or other complications of gallstone disease, without adding risks due to a more difficult surgical dissection in the early days following pancreatitis [16,18]. Because the current literature may be flawed by selection bias, a randomized study is needed to confirm that early cholecystectomy is indeed both superior to interval cholecystectomy and safe. The aim of this study is to investigate whether early laparoscopic cholecystectomy, within 72 hours after recovery of a first episode of mild biliary pancreatitis, as compared with interval laparoscopic cholecystectomy, 25 to 30 days after recovery, reduces mortality and acute re-admissions for biliary events.

## Methods/Design

### Design

The PONCHO trial is a randomized controlled, parallel-group, assessor-blinded, superiority multicenter trial. Patients will be randomly allocated to receive early laparoscopic cholecystectomy, within 72 hours after randomization, or interval laparoscopic cholecystectomy, 25 to 30 days after randomization.

### Primary endpoint

The primary endpoint is a composite endpoint of mortality and acute re-admissions for biliary events (that is, recurrent biliary pancreatitis, acute cholecystitis, symptomatic/obstructive choledocholithiasis requiring endoscopic retrograde cholangiopancreaticography (ERCP) including cholangitis (with/without ES), and uncomplicated biliary colics; see Table 1 for definitions) occurring within 6 months following randomization.

**Table 1 T1:** Primary endpoint: definitions of biliary events

**Biliary event**	**Definition**
Biliary pancreatitis	Diagnosis of acute pancreatitis if at least two of the three following features are present [19]:
	1. Upper abdominal pain;
	2. Serum lipase or amylase levels above three times the upper level of normal;
	3. Characteristic findings of acute pancreatitis on cross-sectional abdominal imaging.
	Biliary pancreatitis if one of the following definitions is present [20]:
	1. Gallstones and/or sludge diagnosed on imaging (transabdominal or endoscopic ultrasound or computed tomography);
	2. In the absence of gallstones and/or sludge, a dilated common bile duct on ultrasound (>8 mm in patients ≤75 years old or >10 mm in patients >75 years old);
	3. The following laboratory abnormality: alanine aminotransferase (ALAT) level >2 times higher than normal values, with ALAT >aspartate aminotransferase.
Acute cholecystitis	Defined according to the 2007 Tokyo classification, grade I to III [21,22].
	A. Local signs of inflammation:
	1) Murphy’s sign;
	2) RUQ mass/pain/tenderness.
	B. Systemic signs of inflammation:
	1) Fever;
	2) Elevated C-reactive protein;
	3) Elevated white blood cell count.
	C. Imaging findings characteristic of acute cholecystitis
	Definite diagnosis
	1) One item in A and one item in B are positive;
	2) C confirms the diagnosis when acute cholecystitis is suspected clinically.
Biliary colic	Upper abdominal pain (either right upper quadrant or epigastric pain) lasting at least 30 minutes, according to the Rome criteria [22].

### Secondary endpoints

We hypothesize that early laparoscopic cholecystectomy is both effective and safe and therefore included the following secondary endpoints to assess such an effect: individual endpoints of the composite endpoint; cholangitis (Table 2); number of biliary colics registered in patient diary; difficulty of cholecystectomy (scored by visual analog scale 0 to 10; 5 being averagely difficult); conversion to open cholecystectomy (measure of technical difficulty); total length of hospital stay; need for ICU admission and total length of ICU stay; and total direct and indirect costs.

**Table 2 T2:** Secondary endpoint: definitions

**Biliary event**	**Definition**
Cholangitis	All of the following features (as previously defined) [20]:
	1) Serum total bilirubin level >40 μmol/l (>2.3 mg/dl) and/or dilated common bile duct (>6 mm) on transabdominal or endoscopic ultrasound or computed tomography;
	2) Temperature >38.5°C.
Organ failure	Failure of one or more of the following organ systems [19]:
	1) Respiratory: PaO_2_ ≤60 mmHg or need for mechanical ventilation;
	2) Cardiovascular: systolic blood pressure <90 mmHg or need for catecholamine support;
	3) Renal: creatinine level >177 μmol/l after rehydration or need for hemofiltration or hemodialysis (not including pre-existent renal failure).
Biliary leakage	Defined according to the Amsterdam criteria [23]:
	Type A: cystic duct leaks or leakage from aberrant or peripheral hepatic radicals;
	Type B: major bile duct leaks with or without concomitant biliary strictures;
	Type C: bile duct strictures without bile leakage;
	Type D: complete transection of the duct with or without excision of some portion of the bile duct.

### Safety endpoints

The safety endpoints are: biliary leakage, Amsterdam types A to D (Table 2) [23]; need for additional surgical, radiological or endoscopic interventions [23]; other complications requiring treatment (that is, bacteremia or pneumonia); bleeding requiring reoperation or blood transfusion; and new-onset organ failure (Table 2).

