### Treatment protocol

Group A received early laparoscopic cholecystectomy, within 72 hours after randomization (Figure 2).

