**Figure 2 F2:**
[figure not shown]
PONCHO overview of eligibility and group allocation.

As can be seen in the time of randomization criteria, patients will be randomized 1 or 2 days prior to discharge in an attempt to prevent prolonged hospital stay due to a waiting time for cholecystectomy.

Group B received interval laparoscopic cholecystectomy, 25 to 30 days after randomization (Figure 2).

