### Safety

An independent Data and Safety Monitoring Committee (DSMC) will evaluate the progress of the trial and will examine safety variables. Every 30 patients, individualized patient description charts including unblinded safety parameters will be presented to the DSMC. In addition to the safety endpoints, death and (serious) adverse events, the incidence of biliary leakage, Amsterdam type D [23], will be of special interest. Extra monitoring of this severe complication is clinically important. The incidence of bile duct injury (Amsterdam types A to D) has a range between 0.16 and 1.5% in the Netherlands [21].

After full explanation of the data presented by the investigators, the members of the DSMC will discuss the consequences of the data presented in the absence of the investigators. Adverse events are defined as ‘any undesirable experience occurring to a subject during a clinical trial, whether or not considered related to the intervention’ (that is, early cholecystectomy). All involved physicians will repetitively be asked to report any potential adverse events. These adverse events will be listed and discussed by the DSMC. The outcome of the meeting of the DSMC will then be discussed with the trial steering committee. The outcome will also be sent to the Institutional Review Board of the Radboud University Nijmegen Medical Centre. All possible severe adverse events will be reported to the Central Committee on Research involving Human Subjects (Centrale Commissie Mensgebonden Onderzoek) and the Institutional Review Board using the online module [37].

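### Three of the five safety endpoints are not tied to the cholecystectomy, so disease events during the wait count against the interval arm and dilute any excess of surgical complications after early surgery

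*Protocol article*

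**What the plan says.** The Abstract (Background) of the protocol article sets a hypothesis with a safety limb: early surgery should bring its benefit "without increasing the difficulty of dissection and the surgical complication rate compared with interval laparoscopic cholecystectomy".

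The difficulty half of that limb is covered under Secondary endpoints by a visual analog score and by conversion to open surgery. The complication half rests on the list under Safety endpoints. Besides biliary leakage and bleeding, that list has three items:

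- "need for additional surgical, radiological or endoscopic interventions";
- "other complications requiring treatment (that is, bacteremia or pneumonia");
- "new-onset organ failure (Table 2").

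None of the three names the operation, a cause or a starting point. Table 2 defines organ failure by physiological thresholds only.

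Under Treatment protocol, "Group A received early laparoscopic cholecystectomy, within 72 hours after randomization", while "Group B received interval laparoscopic cholecystectomy, 25 to 30 days after randomization". The Analyses section makes every analysis intention-to-treat. It also says that primary, secondary and safety endpoints will be pooled to compare the two strategies. Blinded adjudication is described there for the primary endpoint only.

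**The concern.** Biliary disease continues in one arm for about four weeks after it has largely been removed as a cause in the other. If a safety endpoint counts any intervention, any treated infection or any new organ failure, the illness that early surgery is meant to prevent enters the measure meant to detect its harm.

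The overlap is most direct for one primary component, "symptomatic/obstructive choledocholithiasis requiring endoscopic retrograde cholangiopancreaticography (ERCP) including cholangitis (with/without ES"). That ERCP is an endoscopic intervention, so read literally it can count once for efficacy and once for safety, before the interval patient has had a cholecystectomy.

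At stake is the trial's answer to surgeons' main worry. The Discussion names a harder operation with possibly more complications as the first potential downside of operating early. An excess of that kind could be offset by waiting-period illness in the comparator and read as no difference in surgical complications.

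**Working it through.** **The plan's own figure.** The sample size section uses 8.2% against 1.0%, two-sided 5%, 80% power. With pooled variance and no continuity correction:

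n = [1.960 × √(2 × 0.046 × 0.954) + 0.842 × √(0.082 × 0.918 + 0.010 × 0.990)]² / 0.072² ≈ 131.7, so 132 per group.

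264 / 0.995 = 265.3, so 266 in total. Both figures reproduce and are not in dispute.

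**Expected disease events before interval surgery.** The same section gives 6.0% re-admitted within 4 weeks before cholecystectomy (5% with recurrent pancreatitis), plus 1.2% for missed events: 6.0 + 1.2 = 7.2%. With 266 / 2 = 133 per arm, 133 × 0.072 = 9.6 interval patients. The early arm is operated on within 72 hours, so its share is taken as zero. The further 1% after cholecystectomy is set for both arms and does not separate them.

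**Which endpoints can pick these up.**

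| Endpoint | Tied to the operation? |
|---|---|
| Biliary leakage, Amsterdam A to D | In effect yes |
| Bleeding requiring reoperation | Yes |
| Bleeding requiring transfusion | Only in part |
| Additional interventions | No |
| Bacteremia or pneumonia | No |
| New-onset organ failure | No |
| Conversion, difficulty score (secondary) | Yes |

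**Dilution.** Let s be the operative complication rate in the interval arm, R the true operative risk ratio for early against interval surgery, and w the share of interval patients with a disease-caused safety event during the wait. The protocol gives none of these, so all are assumptions. Treating operative and waiting-period events as independent:

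- early arm: R × s
- interval arm: 1 − (1 − s)(1 − w)
- apparent risk ratio: the first divided by the second

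If a quarter or a half of the 7.2% lead to a safety-type event, w = 1.8% or 3.6%, that is 133 × 0.018 = 2.4 or 133 × 0.036 = 4.8 patients. For s = 5%, R = 2 and w = 1.8%: 0.10 / (1 − 0.95 × 0.982) = 0.10 / 0.0671 = 1.49.

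| s | true R | w = 1.8% | w = 3.6% | w = 5.4% | w = 7.2% |
|---|---|---|---|---|---|
| 5% | 2.0 | 1.49 | 1.19 | 0.99 | 0.84 |
| 3% | 2.0 | 1.26 | 0.92 | 0.73 | 0.60 |
| 5% | 3.0 | 2.24 | 1.78 | 1.48 | 1.27 |

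The last column would require every waiting-period re-admission to bring a safety-type event, so it is an upper bound. A true doubling at s = 5% vanishes when 1 − w = 0.90 / 0.95, so w = 5.3%.

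**Power with 133 per arm (normal approximation).** For s = 5% and R = 3, power falls from 78% with w = 0 to 59% at w = 1.8% and 39% at w = 3.6%. For s = 5% and R = 2, it is only 34% even with w = 0.

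**The case against.** **The strategy comparison is legitimate.** The protocol calls the trial pragmatic, and organ failure during the wait is real harm of the interval strategy. This stands, and the all-cause total should stay. It answers which strategy carries more morbidity, which is not the stated hypothesis on surgical complications.

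**The interventions item may be narrower than it reads.** It shares a citation with biliary leakage, so it may have been meant for interventions after surgery or for duct injury. That is possible, but the text does not say so, and the infection and organ failure items have no such citation.

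**A condensed article may leave windows and relatedness to fuller documents.** In part this stands: those may already hold the split. The point here is what the endpoints, as stated, count.

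**The trial is too small to settle surgical harm anyway.** At 3% against 6%, power is about 22% without any dilution, so a non-significant result is likely either way. This stands, but it makes an estimate undistorted by waiting-period illness more useful.

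**Stronger readings that the document does not support.**

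- A reader might infer that every safety endpoint is affected. Amsterdam-type leakage and bleeding requiring reoperation presuppose surgery, and the quoted 0.16 to 1.5% range for bile duct injury is not what is diluted.
- Post-operative observation to 6 months differs (about 181 against 155 days, at mid-window surgery dates), but both far exceed a window such as 30 days.
- At data monitoring reviews, some recently randomized interval patients will not yet have been operated on. That is inherent in the design. The committee sees unblinded individual charts, and suspected harm leads to a discussion of causality.

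**Conclusion.** The point holds for three of the five safety endpoints, and in part for transfusion. Under intention-to-treat, disease events during the wait fall almost only in the interval arm. They pull the comparison of surgical complications in favour of early surgery, and one ERCP can count for both efficacy and safety.

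The direction follows from the text. The size does not: only the 7.2% comes from the protocol, while the operative rate, the true risk ratio and the share of re-admissions that produce a safety event are assumed. On a 5% operative rate and a true risk ratio of 2.0, an apparent 1.49 to 1.19 is a reasonable illustration. A reader might go on to infer that a real excess would be hidden altogether; that occurs only for some assumed values and is not established.

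The primary endpoint and the sample size are untouched. This is a cheap improvement to the safety analysis, not a flaw in the trial's main comparison.

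**What to change.** For the surgical-complication hypothesis, add a comparison by allocated arm of safety events from the start of cholecystectomy over the same fixed window in both arms, for example 30 days. Use all randomized patients as denominator, with operated patients as a sensitivity analysis. Report safety-type events before the operation separately as waiting-period morbidity. Keep the all-cause total from randomization as the strategy-level summary, and state that an ERCP already counted in the primary endpoint may also appear in it.

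The cost is a few lines of wording and one extra table. Time to cholecystectomy is already to be reported, so the date of surgery is recorded; event dates are the only other need, and no judgement of causality is required. The operated-only version conditions on something that happens after randomization, since a recurrence may delay or prevent surgery. It must therefore be read beside the all-randomized result.

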### Study population

All adult patients admitted with a first episode of biliary acute pancreatitis to one of the 18 participating hospitals of the Dutch Pancreatitis Study Group (listed in Authors’ information) will be assessed for eligibility during their hospital admission. Potentially eligible patients are followed until eligibility is established 1 or 2 days before discharge from the hospital. If patients are classified as having mild biliary pancreatitis and fulfill all inclusion and exclusion criteria they are randomized (with a 1:1 ratio and stratified for hospital and ES) to undergo early laparoscopic cholecystectomy or interval laparoscopic cholecystectomy (Figure 1).

**Figure 1 F1:**
[figure not shown]
**Flow of participants in the PONCHO trial. **According to CONSORT [24].

### Inclusion criteria

Inclusion criteria are: age ≥18 years; diagnosis of acute pancreatitis (at least two of the three following features present [19]: upper abdominal pain; serum lipase or amylase levels above three times the upper level of normal; and characteristic findings of acute pancreatitis on cross-sectional abdominal imaging); mild pancreatitis (fulfilling both [19]: no pancreatic necrosis and/or peripancreatic collections; and no persistent (> 48 hours) organ failure (Table 2)); and biliary pancreatitis (any of the following three definitions [20,25-29]: gallstones and/or sludge diagnosed on imaging (transabdominal or endoscopic ultrasound or computed tomography); in the absence of gallstones and/or sludge, a dilated common bile duct on ultrasound (>8 mm in patients ≤75 years old or >10 mm in patients >75 years old); and alanine aminotransferase level >2 times higher than normal values, with serum alanine aminotransferase levels >aspartate aminotransferase level); and written informed consent.

### Exclusion criteria

Exclusion criteria are: American Society of Anesthesiologists (ASA) III patients >75 years old; ASA IV and V patients; patients with ongoing alcohol abuse or chronic pancreatitis (males >3 units per day, females >2 units per day) [30]; or pregnancy.

### Time of randomization

After eligibility has been confirmed and written informed consent has been obtained, randomization will take place when the following five discharge criteria are met: the treating physician anticipates that the patient can be discharged within 1 or 2 days; no need for opioid analgesics; declining C-reactive protein levels and <100 mg/l; no evidence of local or systemic complications (for example, no fever); and the patient has resumed oral intake.

### Randomization

Randomization is possible 24 hours per day, 7 days per week and is performed centrally by the study coordinator using an Internet randomization module (Clinical Research Unit, Academic Medical Center, Amsterdam, the Netherlands). Randomization is stratified according to whether ES is performed and according to hospital.

Randomization is balanced for ES because ES has a protective effect on the occurrence of recurrent biliary pancreatitis and common bile duct obstruction [31]. This allows for subgroup analysis with or without ES. Randomization is balanced per hospital as treatment strategies, such as the use of intraoperative cholangiography, indication for enteral feeding and endoscopic sphincterotomy, may differ between hospitals.

Permuted-block randomization with varying block size is used and block size is concealed to all investigators involved in this study. Using this method it is impossible for investigators to predict the allocation of trial participants. Concealing the allocation for investigators or trial participants is unfeasible due to the nature of this trial, because trial participants need to be scheduled for an early or interval cholecystectomy.

